### Recruitment

Participants will be recruited in 13 hospitals (Supplementary File 2). Patients willing to participate in the trial will be screened for eligibility by a clinical researcher. Eligible patients will receive detailed information about the clinical trial. Patients providing consent to the clinical study terms will participate in the trial and will be randomly assigned to the QDG or control group.

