### Randomization and blinding

Participants will be randomized in a 1:1 ratio to the QDG or control group using a computer-generated, site-stratified, block randomization schedule. The study drugs will be labeled with sequential randomization numbers, and the participant will be assigned the lowest number available at each hospital. All participants, care providers, and attending physicians will be blinded to the assignment until the trial is finished. The trial-group assignment will be concealed from all participants, clinicians, and investigators throughout the trial. To ensure blinding, randomization sequences will be generated by statisticians and then kept in identical, opaque, sealed, sequentially numbered envelopes. Only the trial’s pharmacist has access to the randomization list.

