### Intervention

The course of treatment will last 4 weeks, and patients will be followed up for 4 additional weeks to assess any persistent effects of the drug. Participants will be examined at week 0 (baseline, visit 2), week 4 (end of treatment, visit 3), and week 8 (end of follow-up, visit 4). The QDG group will be treated with valsartan capsule simulation agent (80 mg, once daily for 4 weeks) and QDG (5 g, twice daily for 4 weeks), while the control group will be treated with valsartan capsule simulation agent (80 mg, once daily for 4 weeks) and QDG simulation agent (5 g, twice daily for 4 weeks). The drugs and simulation agents will be provided by Jiangyin Tianjiang Pharmaceutical (Jiang’yin City, China). The simulation agent will be prepared using soluble starch, colorant, and a bitter additive to achieve appearance, smell, and taste comparable to the drug. The drugs and simulation agents will be identical in outer packaging, color, shape, and flavor. The drug that patients did not take would be returned to the researcher. And no other anti-hypertension drugs should be taken during the study process.

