### Outcomes assessment

#### Primary outcome

After 4 weeks’ treatment, the decreased values of clinic systolic blood pressure and diastolic blood pressure after treatment are used as primary outcome (the difference between visits 3 and 2). Clinic blood pressure was measured using an automated sphygmomanometer (Omron, HEM-7121) in the right arm with an appropriate cuff size. The measurements were taken after the participants rested in a sitting position for 5 min, at least 1 h after the subject’s last meal, and at least 30 min after smoking or consuming caffeinated beverages. To obtain accurate data, the measurements will be conducted 3 times, and the mean value will be used as the outcome.

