### Statistical analysis

The data analysis will be based on the principle of intention to treat (ITT), and potential missing values will be filled in using data from the last observation. Data will be presented as mean ± standard deviation, median with range, or number and percentage. Data will be analyzed using SAS 9.3 software (SAS Institute, Cary, NC, USA) using two-sided tests and a significance level of *p* < 0.025. For comparison between groups, two independent sample *T*-test (group *T*-test ) and Wilcoxon rank sum test were used for measurement data. The Pearson chi-square test or Fisher exact test was used for counting data. Wilcoxon rank sum tests were used for grade data. For intra-group comparison, paired *T*-tests or Wilcoxon symbolic rank test was used for measurement data. CMH chi-square tests were used when considering the central effect. Sub-group analyses will be conducted based on the characteristics of included participants.

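### The primary comparison leaves out site and baseline blood pressure as covariates, so it may give up precision that data already collected could recover

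*Protocol article*

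**What the plan says.** All references are to the protocol article.

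- **Design.** Under Randomization and blinding, allocation is 1:1, made "using a computer-generated, site-stratified, block randomization schedule". Under Recruitment: "Participants will be recruited in 13 hospitals".
- **Primary outcome.** The fall in clinic systolic and diastolic pressure over 4 weeks, defined as "the difference between visits 3 and 2". The Intervention section makes visit 2 the baseline examination, so a baseline value is collected for every participant and is subtracted in forming the outcome.
- **Analysis.** Under Statistical analysis, the between-group rule is "two independent sample *T*-test (group *T*-test ) and Wilcoxon rank sum test were used for measurement data". No ANCOVA, regression or mixed model is named.
- **Centre.** The same section adds "CMH chi-square tests were used when considering the central effect".
- **Margin and planning values.** Under Sample size, the margin is -3 mm Hg, and the assumed systolic falls are 12.0 (SD 10.5) on QDG and 12.9 (SD 11.8) on valsartan.

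The article does not say how the t-test result becomes a non-inferiority statement. It mentions no confidence interval for the primary comparison.

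**The concern.** When treatment is balanced within site by design, a pooled two-sample test does not use that balance: any real difference between sites in blood pressure change stays in its standard error. A raw change score also fixes the baseline slope at 1. If the true slope differs from 1, adjusting for baseline removes further variance, together with whatever chance baseline imbalance the subtraction leaves behind.

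Non-inferiority is decided by where one confidence bound falls relative to the margin, so unnecessary width costs power directly. CMH chi-square does not fill the gap, because it returns a stratified test and not a site-adjusted difference in mm Hg. The plan thus recognises centre as relevant but names no method that brings it into the primary estimate. This is a stated choice that fits the design poorly, and not a detail left for a fuller document.

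**Working it through.** **Inputs from the Sample size section.** SDs 10.5 and 11.8; assumed difference 12.0 - 12.9 = -0.9 mm Hg; margin -3 mm Hg; 440 participants needed; 552 to be recruited (276 per arm).

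**Inputs not in the article (assumed).** The share of variance in change explained by baseline and site together (R2), the between-site correlation (ICC), the baseline SD, and the baseline to follow-up correlation (rho).

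**1. The plan's own figure.** Sum of variances: 10.5² + 11.8² = 110.25 + 139.24 = 249.49. Distance to the margin: -0.9 - (-3) = 2.1. The printed formula at one-sided 0.05 and 80% power gives (1.645 + 0.842)² × 249.49 / 2.1² = 350 per arm, or 700 in total, not 440. A total near 440 appears only with one-sided 0.025 and no assumed difference (218 per arm, 436 in total). That discrepancy is a separate and larger problem. It is shown here because it sets the baseline power below.

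**2. Standard error with 276 per arm.** SE = sqrt(249.49 × (1 - R2) / 276).

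- R2 = 0: 0.951 mm Hg
- R2 = 0.25: 0.823 mm Hg, equivalent to 276 / 0.75 = 368 per arm without adjustment

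**3. Power at the planning difference.** Power = Phi(2.1 / SE - z). The article's alpha can be read in more than one way, so three levels are shown.

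| Level | z | R2 = 0 | R2 = 0.25 |
|---|---|---|---|
| One-sided 0.05 (formula as printed) | 1.645 | 71% | 82% |
| One-sided 0.025 | 1.960 | 60% | 72% |
| Two-sided p < 0.025 taken literally (0.0125 per side) | 2.241 | 49% | 62% |

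**4. Where the gain could come from.** With 220 per arm (440 analysed), the unadjusted SE is sqrt(249.49 / 220) = 1.065 and the 95% half-width is 1.96 × 1.065 = 2.09 mm Hg.

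- *Site alone.* The variance factor is 1 - ICC. ICC 0, 0.02, 0.05 and 0.10 give half-widths of 2.09, 2.07, 2.03 and 1.98: 0 to 5% narrower.
- *Baseline alone.* The variance factor is (1 - rho²) / (1 + k² - 2 × rho × k), where k is baseline SD over follow-up SD. With k = 1, rho of 0.3, 0.5 and 0.7 gives 1.68, 1.81 and 1.92: 8 to 19% narrower. With k = 0.6, rho of 0.3, 0.5 and 0.6 gives 1.99, 2.07 and 2.09: 0 to 5% narrower.

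The case k = 1, rho = 0.5 has a factor of 0.75, which is R2 = 0.25. Lower correlations with equal SDs would give more. The case k = 0.6, rho = 0.6 has a slope of rho / k = 1 and gives no gain.

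**5. Simulation check.** With 13 sites, blocking within site and about 440 participants, the unadjusted half-width was 2.08 to 2.09 mm Hg. The half-width adjusted for site and baseline was 1.72 to 2.10. With ICC 0 and slope 1 the two were the same to within 0.002 mm Hg. Coverage of the unadjusted 95% interval was 0.948 to 0.963, so it was valid and slightly conservative where sites differed.

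**The case against.** The strongest defence is that nothing here is invalid. A t-test after site-stratified randomisation does not inflate the type I error and does not bias the estimate; if anything it is conservative. That stands, and it makes this a point about efficiency.

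The size of the gain also cannot be derived from the article. It may be nil. Enrolling only grade 1 hypertension narrows the range of baseline pressure, which pushes the baseline gain towards the low end. That stands too, and is why the range above starts at zero.

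Baseline is already subtracted, so it would be wrong to say that baseline imbalance is left wholly uncorrected. Only the part that arises from a slope other than 1 remains.

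It can further be said that the CMH sentence is not confined to count data, and that the CMH family includes stratified mean-score tests. This narrows the criticism without removing it: a stratified test still supplies no adjusted mean difference or bound to compare with -3 mm Hg.

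Finally, replacing a pre-specified test at the analysis stage with one that tends to narrow the interval carries a credibility cost in a non-inferiority trial. Trial status puts the trial in data analysis, and Interim analysis provides for a look at the primary outcome after one year. This objection stands and shapes the fix.

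A reader might also infer that hormone comparisons suffer from differences between hospital laboratories. The article does not support this. The statement about hospital laboratories is in the Safety section and concerns samples for hepatic and renal function. Secondary outcomes says only that hormones are measured by immunoassay and names no laboratory.

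**Conclusion.** The point holds as one of recoverable precision. The named primary analysis uses neither the stratification factor nor baseline as a covariate, and the centre method named cannot produce the estimate that a non-inferiority decision needs.

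The size is conditional. If site and baseline explain 0 to 25% of the variance in change, the SE with 276 per arm falls by 0 to 13% (0.823 / 0.951 = 0.865). Power then rises by between 0 and about 10 to 13 percentage points, depending on how alpha is read. The lower end applies if sites do not differ and the slope on baseline is near 1.

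Two stronger readings should be resisted. The t-test does not make the trial's conclusion invalid. Nor does it cause the low power at the planning difference: that comes from a sample size the printed inputs do not reproduce, and adjustment could at best recover part of it.

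**What to change.** Make the primary analysis an ANCOVA of 4-week change on treatment, the outcome's own baseline and site, for systolic and for diastolic pressure, with small sites pooled by a rule set in advance. Compare the adjusted confidence bound for systolic pressure with -3 mm Hg, at an alpha level that reconciles the Sample size and Statistical analysis sections. Use the same model for the continuous secondary outcomes, and report the two-sample t-test as a sensitivity analysis.

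No new data are needed, and at 440 to 552 participants the extra parameters cost almost nothing. The real cost is timing. Recruitment has ended and the article reports data analysis under way, so the model should be fixed and dated before unblinding. If that is no longer possible, report it openly as a post hoc change beside the pre-specified t-test.

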## Abstract

**Background:**

Numerous pre-clinical studies showed that Qingda granule (QDG) was effective in treating hypertension. This study aims to evaluate the efficacy and safety of QDG in reducing blood pressure among patients with grade 1 hypertension at low-medium risk.

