**Methods:**

The study is designed as a randomized, multi-center, double-blinded, non-inferiority clinical trial. Five hundred fifty-two patients with grade 1 hypertension at low-medium risk from 13 hospitals will be recruited and randomly assigned to the QDG group (*n* = 276, treated with valsartan capsule simulation agent and QDG) or control group (*n* = 276, treated with valsartan capsule and QDG simulation agent). The treatment period will be 4 weeks and the follow-up period will last 4 weeks after treatment. Primary outcome will be a decreased value of systolic blood pressure and diastolic blood pressure after treatment. And second outcome will include the decreased value of diastolic blood pressure and systolic blood pressure at the end of follow-up, the percentage of participants achieving normal blood pressure at the end of treatment and follow-up, the Hamilton Anxiety Scale and TCM syndrome scores at the end of treatment and follow-up, and levels of hypertensive hormones at end of treatment and follow-up.

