### Participants

Inpatients and outpatients diagnosed with grade 1 hypertension (at low-medium risk) from 13 hospitals (Supplementary File 2) will be screened based on the inclusion and exclusion criteria. The researchers will recruit inpatients and outpatients and gain the informed consent from the patients during the admission to the outpatients or to the hospital.

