### Sample size

The target sample size was calculated according to the decreased value of systolic blood pressure (12.9±11.8 mm Hg) observed after 8-week treatment with valsartan capsules in a randomized clinical trial [16], and the non-inferiority margin of QDG has been established as −3 mm Hg. The decreased value of QDG on systolic blood pressure was 12.0±10.5 mm Hg, which was calculated based on our clinical practice. The minimal sample size to achieve a type I error rate of *α* = 0.05 and a power of 80% (type II error rate *β* = 0.2) is 440 participants. The size was calculated using the formula:$$n=\frac{{\left({Z}_{1-\alpha }+{Z}_{1-\beta}\right)}^2\times \left({\upsigma}_1^2+{\upsigma}_2^2\right)}{{\left(\varepsilon -\delta \right)}^2}$$where σ_1_ and σ_2_ are the standard deviations of the QDG and control groups, respectively; *ε* is the mean difference between the two groups; δ is the non-inferiority margin; *α* is the type I error rate; and *β* is the type II error rate. The study will strive to enroll 550 participants to compensate for a dropout rate as high as 20%. For convenience of randomization, we will aim to recruit 552 patients.

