## Discussion

QXJYT was created by Academician [name]. After years of clinical practice, it has been proved to have a certain antihypertensive effect, which can significantly improve the clinical symptoms and quality of life of hypertension. At the same time, it has an obvious protective effect on target organs [17]. QDG is composed of *Gastrodia elata*, *Uncaria*, *Scutellaria baicalensis*, and *lotus seed heart* according to more than 60 years’ clinical experience of Academician [name] in addition and subtraction of QXJYT [18]. In the present clinical trial, the effects of QDG on grade 1 hypertension (low-medium risk) will be investigated. QDG, derived from QXJYD, showed obvious effects on decreasing blood pressure and promoting the vasorelaxation of thoracic aortic rings in spontaneously hypertensive rats [10]. Further mechanistic investigation demonstrated that QDG ameliorated Ang II-induced hypertension in mice and inhibited proliferation of vascular smooth muscle cell of aorta via suppressing the activation of MAPKs and PI3K/AKT pathways [19]. In addition, some components of QDG, such as rhynchophylline, gastrodin, and baicalin, also have the effects of antihypertension [9, 11, 12]. These results serve as a solid foundation for the present clinical trial investigating the effects of QDG on grade 1 hypertension with low-medium risk. The present clinical study is designed as a randomized, multi-center, double-blinded, placebo-controlled, non-inferiority trial, which will provide high-quality evidence for the further clinical practice of QDG.

The clinical trial will be performed in China and will enroll Chinese patients, and the 13 hospitals will mainly serve Han Chinese, so it will not evaluate the effects of QDG in other ethnic groups. The follow-up period is relatively short, and therefore, some effects may be potentially missed.

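### Within-arm paired tests are planned at p < 0.025 and not marked descriptive; against a valsartan control they cannot show that QDG itself lowers blood pressure, and the placebo-controlled label must be reconciled with the control arm.

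*Protocol article*

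**What the plan says.** **Tests.** The Statistical analysis section lists between-arm tests ("For comparison between groups, two independent sample" t-tests and rank sum tests) and then within-arm tests: "For intra-group comparison, paired *T*-tests or Wilcoxon symbolic rank test was used for measurement data". The level is set once for all of them, "using two-sided tests and a significance level of" p < 0.025. The article gives the within-arm tests no stated role, whether primary, supportive or descriptive.

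**Aim.** The abstract words it in absolute terms: "This study aims to evaluate the efficacy and safety of QDG in reducing blood pressure among patients with grade 1 hypertension at low-medium risk". The Background section words the objective as a comparison with valsartan.

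**Comparator.** The article describes the control in ways that do not agree:
- Abstract, Methods: "control group (*n* = 276, treated with valsartan capsule and QDG simulation agent", that is, active valsartan with a dummy for QDG.
- Background: valsartan.
- Intervention: the control group receives the dummies of both drugs.
- Discussion: "The present clinical study is designed as a randomized, multi-center, double-blinded, placebo-controlled, non-inferiority trial".

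**Timing.** The primary outcome is the change from visit 2 (baseline) to visit 3 (week 4). A secondary outcome is the change from visit 2 to visit 4, after four weeks off treatment. The Intervention section says that this off-treatment period is there to look for persisting drug effects.

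**The concern.** Participants enter because their pressure is raised, have been off antihypertensive drugs for a month, and may be recruited as inpatients or outpatients ("gain the informed consent from the patients during the admission to the outpatients or to the hospital"). Pressure in such a group can fall on re-measurement through regression to the mean, habituation to measurement or placebo response. A before-after test within one arm adds all of these to any drug effect.

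If the control arm receives valsartan, its fall has the same components plus the valsartan effect, so no arm isolates the non-drug part. The dummies then serve only to mask treatment, and placebo-controlled is the wrong name for the comparison.

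What is at stake is the claim that could be made. An absolute aim in the abstract, a placebo-controlled label and a significant paired p-value in the QDG arm would together invite the statement that QDG lowers blood pressure. At visit 4 they would invite the statement that its effect persists. A valsartan-controlled design supports only a statement relative to valsartan.

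**Working it through.** The article gives no figure for the within-arm tests, so there is none to reproduce. The inputs below are its own except where marked as assumed.

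**Inputs**
- SD of the systolic change on QDG: 10.5 mm Hg (Sample size). For sensitivity, the valsartan SD from the same section: "decreased value of systolic blood pressure (12.9±11.8 mm Hg) observed after 8-week treatment with valsartan capsules".
- n in the QDG arm: 276 randomized (abstract), or 440/2 = 220 after the planned 20% dropout (440/0.8 = 550, as stated).
- Level: two-sided 0.025, so z = 2.241.

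**Step 1: smallest significant mean fall.** Critical fall = 2.241 × SD/√n.
- n = 276: SE = 10.5/√276 = 0.632; critical fall = 2.241 × 0.632 = 1.42 mm Hg.
- n = 220: SE = 10.5/√220 = 0.708; critical fall = 2.241 × 0.708 = 1.59 mm Hg.
- With SD 11.8: 1.59 (n = 276) and 1.78 (n = 220) mm Hg.

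For scale, 1.42 is about one-eighth of the 12.0 mm Hg fall assumed for QDG (1.42/12.0 = 0.12) and under half of the 3 mm Hg margin (1.42/3 = 0.47).

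**Step 2: chance of a significant fall with no drug effect.** Probability = Φ(d/SE − 2.241), where d is an assumed non-drug fall.

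| Assumed d (mm Hg) | n = 276 | n = 220 |
|---|---|---|
| 1 | Φ(1.58 − 2.24) = 0.26 | 0.20 |
| 2 | Φ(3.16 − 2.24) = 0.82 | 0.72 |
| 3 | Φ(4.75 − 2.24) = 0.99 | 0.98 |

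**Step 3: how large could regression to the mean be?** The article gives no source mean, between-person SD or test-retest reliability, so every input here is assumed: selection at 140–159 mm Hg, total SD 15, reliability 0.6 to 0.9, zero drug effect, n = 276. Simulated results when the reading used for selection is also the baseline:

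| Source mean (mm Hg) | Expected fall (mm Hg) | Chance of a significant fall |
|---|---|---|
| 120 to 135 | 1.3 to 10.5 | 85% to 100% |
| 145 | 0.4 to 1.7 | 12% to 54% |
| 150 (middle of the window) | 0 | about 1% |

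When eligibility is set on an earlier reading and baseline is a fresh one, the expected fall after baseline from regression to the mean is about zero at every setting.

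**Step 4: the comparator.** The abstract and Background sections describe an active control. Read literally, the Intervention section describes a control with no active drug, and the Discussion label fits that reading. On the first reading the paired test cannot isolate a QDG effect. On the second, the between-arm difference would itself estimate it, and the paired test would add nothing. Neither reading gives the paired p-value an inferential use.

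**The case against.** The strongest reply is that nobody has said the paired tests carry the efficacy claim, and that is correct. The article defines a randomized non-inferiority trial, sizes it on the between-arm difference with a 3 mm Hg margin, and in the Background section already frames the objective against valsartan. Any non-drug fall is equal in expectation in both arms, so the randomized comparison is not biased by it. Harm would need a use of the paired tests that the article does not announce.

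The second reply is that regression to the mean may be small here, and this also stands. Baseline is numbered visit 2, so an earlier visit exists that the text does not describe, and the schedule figure is not shown. If eligibility was settled at that visit and pressure was measured afresh at visit 2, regression to the mean is about zero. Clinic pressure is the mean of three rested readings, which limits measurement noise. That no run-in is described proves little in a condensed article. Nor does the text say that baseline was taken in hospital and week 4 at home, so a fall from leaving hospital is conjecture.

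A reader might therefore infer that the paired tests are bound to be significant through regression to the mean alone. The documents do not support that: the chance ran from about 1% to 100% over the assumed settings. A reader might also infer that the trial certainly has no placebo arm, but the Intervention section taken literally says otherwise.

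These replies limit the point without removing it. Habituation and placebo response remain even with a fresh baseline, the tests are planned at the same level as the between-arm tests with no descriptive label, and the descriptions of the control arm conflict.

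**Conclusion.** The point holds in a limited form. The article plans within-arm tests at two-sided 0.025 without restricting their use. Under the valsartan comparator of the abstract and Background, such a test in the QDG arm cannot distinguish drug effect from non-drug change. It turns significant at a mean fall of about 1.4 mm Hg (n = 276) or 1.6 mm Hg (n = 220), given the planning SD of 10.5. The probabilities of 0.26, 0.82 and 0.99 at 1, 2 and 3 mm Hg rest on assumed non-drug falls and a normal approximation to the paired test. The article does not say how large that fall is.

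The placebo-controlled label misdescribes a valsartan comparison, and the control arm is not described consistently. The between-arm analysis is unaffected by non-drug change, and no section makes the paired test the efficacy test. The matter concerns what may be concluded and reported. It is worth correcting because the correction costs almost nothing.

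**What to change.** 1. In Statistical analysis, report the within-arm changes (visits 3 and 4 versus visit 2) as means with confidence intervals, drop the paired p-values, and state that no conclusion on efficacy or persistence rests on them.
2. Reconcile the control arm across the abstract's Methods, Background, Intervention and Discussion sections, and make the design label match the comparator actually used.
3. Word the abstract's aim as the Background section does, as a comparison with valsartan, in line with the reconciled comparator.

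The cost is a few sentences and the loss of an uninformative p-value. The randomized comparison and the sample size do not change. According to the Trial status section the trial is at the analysis stage, so the change can still be made in the analysis and the report.
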